# Protecting Adolescents in Low- And Middle-Income Countries from Interpersonal Violence (PRO YOUTH TRIAL): Study Protocol for a Cluster Randomized Controlled Trial of the Strengthening Families Programme 10-14 (“*Familias Fuertes*”) in Panama

**DOI:** 10.1186/s13063-018-2698-0

**Published:** 2018-06-15

**Keywords:** Interpersonal violence, Adolescence, Family skills training programmes, Strengthening Families Programme 10–14 (SFP 10–14), Panama, Low- and middle-income countries, Prevention

## Abstract

**Background:**

Interpersonal violence can significantly reduce adolescents’ opportunities for becoming happy and healthy adults. Central America is the most violent region in the world and it is estimated that adolescents are involved in 82% of all homicides in this region. Family skills training programmes have been designed to prevent interpersonal violence in adolescents. Several studies in high-income countries suggest they are effective. However, there are no published trials assessing effectiveness of these programmes in low- and middle-income countries (LMIC). The aim of this study is to test the effectiveness of the Strengthening Families Programme 10–14 (SFP 10–14 or “*Familias Fuertes*”) in Panama, a LMIC in Central America. An embedded process evaluation will examine the extent to which the intervention is delivered as intended, variation across trial sites, influences on implementation and intervention-context interactions. Cost-effectiveness will also be assessed.

**Methods:**

This is a cluster randomised controlled trial. The 28 townships with the highest homicide rates in Panama will be randomly allocated to implementation of SFP 10–14 alongside services-as-usual or to services-as-usual only. Approximately 30 families will be recruited in each township, a total sample of 840 families. Families will be assessed at baseline, approximately eight weeks after baseline (i.e. post intervention), six months and 12 months after. The primary outcome measure will be the parent reported externalising subscale of the Child Behaviour Checklist at T3 (i.e., which is approximately 12 months after baseline). For the process evaluation, recruitment, attendance, fidelity and receipt will be measured. Qualitative interviews with facilitators, trainers, parents and adolescents will explore barriers/facilitators to implementation and intervention receipt. For the cost-effectiveness analysis, service use information will be gathered from parents and adolescents with a three-month recall period. Costs and consequences associated with implementation of the intervention will be identified.

**Discussion:**

This trial will be the first to evaluate SFP 10–14 in a LMIC. Results have the potential to guide public policies for the prevention of interpersonal violence in Central America and beyond.

**Trial registration:**

ISRCTN Registry, 14023111. Registered on 13 July 2017.

**Electronic supplementary material:**

The online version of this article (10.1186/s13063-018-2698-0) contains supplementary material, which is available to authorized users.

## Background

Central America is the most violent region in the world in terms of interpersonal violence (i.e. child maltreatment, intimate partner violence, youth gang violence and crime) [1]. The homicide rate due to interpersonal violence is 28.5 per 100,000 inhabitants in comparison with 10.9 in Africa, the second highest region [2]. Young people in Central America are disproportionally affected. According to the 2014 report ‘Health for the World’s Adolescents’, interpersonal violence is the leading cause of adolescent mortality and morbidity in Central America [3]. Those aged < 29 years in upper-middle income countries, such as Panama and Costa Rica, are involved in 82% of all homicides [3].

Perpetration and being a victim of interpersonal violence early in life is not only associated with death and physical injuries, but also with behavioural, mental and social consequences which create a burden for health and justice systems [4]. For example, interpersonal violence is associated with risky sexual behaviours, poor school performance, alcohol and drug abuse, which in turn are risk factors for health difficulties such as early pregnancy, HIV, cancer and cardiovascular diseases later in life. Short- and long-term health consequences of interpersonal violence harm individuals, families and communities, compromise economic development of countries in Central America, and place a great burden on international aid from high-income countries [2]. Violence reduction is key for improving worldwide health.

### The role of the family in violence prevention

Healthy family functioning is one of the most crucial factors protecting adolescents from interpersonal violence. Recent reports from the World Health Organization [5, 6] suggest that family social support [7], family cohesion [8], parental monitoring and non-hostile parenting practices are all protective factors of interpersonal violence [9]. While pathways through which family variables lead to perpetration of interpersonal violence have not been definitively described, poor parental communication and problem-solving skills plus family stress (e.g. divorce, high inter-parental conflict) are associated with the highest levels of offences, arrests and convictions in youth [10]. Poor parenting can be understood as a stressor and, in combination with other family stressors (e.g. divorce, domestic abuse), it accentuates problem behaviours of adolescents. On the other hand, good parenting may serve as a buffer for family stressors.

Based on this literature, family skills training programmes have been developed since the 1980s and are considered among the most effective strategies to prevent interpersonal violence [11]. They are designed to strengthen family protective factors such as communication, trust, problem-solving skills and conflict resolution, and often include opportunities for parents and children to spend positive time together, as ways to strengthen the bonding and attachment between the two.

Most family skills training programmes are mainly used for universal prevention. In other words, they target whole populations (e.g. entire schools or neighbourhoods) without any specific consideration to the risk level present. The idea is that anyone can benefit from prevention efforts with a health promotion orientation and the approach benefits from being non-stigmatising.

### The Strengthening Families Programme 10–14

The Strengthening Families Programme 10–14 (SFP 10–14) is one family intervention with evidence of effectiveness for reducing youth violence in the United States [12]. SFP 10–14 is skill-oriented with underpinnings in theories of bio-psychosocial vulnerability [13] and resilience [14]. It was developed to address risk and protective factors at the individual and family level. It is offered as a seven-session universal package (i.e. targeting all levels of risk) for the transition from childhood into early adolescence (ages of 10–14 years).

Blueprints on Violence Prevention ranks SFP 10–14 as a preventive package with ‘evidence of benefits-minus-costs’ and ‘promising’ impact because of its clear logic model, the validity and reliability of its evaluation findings, its significant positive effects on intended outcomes and its readiness for dissemination [15]. According to its logic model, developing skills in adolescents and parents leads to short-term family and individual changes such as better family functioning, less parental stress, better skills for social interaction in youth and less favourable attitudes towards violence and substance use. These proximal outcomes could then lead to long-term public health changes such as reduced criminality, delinquency and less substance use in communities.

Evaluations of SFP 10–14 in the United States suggest medium to high effect sizes of the programme on adolescent exposure to illicit substance use and young adult lifetime substance use (d = 0.40–0.50). However, there is only one trial evaluating effects of the programme on aggressive and hostile behaviours of adolescents. This trial suggests significant improvements in observer ratings of adolescent aggressive and hostile behaviours when interacting with their parents, in family-member reports of aggressive and hostile behaviours, and in adolescent self-report of aggressive and destructive conduct across settings at 1.5, 2.5 and 4 years after the programme [12].

Besides studies in the United States, SFP 10–14 has been evaluated in Germany [16], Wales [17], Poland [18] and Sweden [19], but until now no evaluation has been conducted in a low- and middle-income country (LMIC) where interpersonal violence rates are high. In addition, more trials of SFP 10–14 are needed, given that no evaluations in high-income countries other than the United States have found positive effects of the programme on alcohol use-related outcomes or on family relationships and functioning.

### The Strengthening Families Programme 10–14 in Panama

Since 2009, the United Nations Office on Drugs and Crime (UNODC) has invested significantly in promoting evidence-based prevention in LMICs using a top-down and a bottom-up approach [20]. Their top-down approach involves engaging directly with policy makers in order to change their views and priorities and ensure their understanding of prevention principles guided by the International Standards on Drug Use Prevention. This entails: (1) explaining the aetiology upon which prevention interventions should be based; (2) explaining the science of prevention; (3) identifying effective evidence-based prevention interventions and the characteristics that make them effective; (4) identifying ineffective interventions; and (5) indicating what makes an effective system of prevention interventions. The aim of UNODC’s approach with policy makers is to ensure service providers at the ‘bottom’ level have access to evidence-based interventions. On the other hand, UNODC’s bottom-up approach focuses on piloting evidence-based preventive interventions adapted to national needs and documenting evaluation reports on their process of implementation, effectiveness and cost-effectiveness [20]. The main social institution of this bottom-up approach is the family. Among the family skills programmes being piloted in Central America is SFP 10–14. Panama was the first country from the Central American region where SFP 10–14 pilots were initiated with UNODC’s support.

The SFP 10–14 programme was originally translated and adapted to the Latin American context by the Pan American Health Organization (PAHO) in close collaboration with its developers. The culturally adapted version of SFP 10–14 was referred to as *Familias Fuertes*. However, for its pilot in Panama, UNODC undertook a cultural review of *Familias Fuertes* and conducted further adaptations to ensure its fit to the local context. These adaptations consisted of changing only names and examples. There were no changes affecting the structure, content or the order of the sessions. Since 2009, the intervention has been delivered to 432 Panamanian families and there are approximately 152 accredited facilitators and 27 local trainers.

UNODC conducted pre-post evaluations of SFP 10–14 in Panama, Honduras and Guatemala that suggested reductions in parental violence towards adolescents and improvements in adolescents’ attitudes towards others after participation in the programme. In addition, in 2012 qualitative evaluations with 30 Panamanian parents who took part in the intervention were conducted to explore acceptability and satisfaction. Results were positive, suggesting the intervention was satisfactory to parents and addressed their concerns in a culturally sensitive manner [21, 22].

Given the lack of rigorous data regarding the effectiveness of SFP 10–14 to prevent violence in LMIC and building on previous efforts by UNODC to adapt and implement the programme in Central America, the main aim of the present project will be to test effectiveness of the culturally adapted version of SFP 10–14 in Panama. We will build on UNODC’s previous investments by evaluating implementation of SFP 10–14 in existing health and educational services across Panama in close partnership with local institutions. This will be the first implementation trial of SFP 10–14 in a LMIC. We chose Panama for this evaluation because, first, UNODC has its main physical base for Central America and the Caribbean in this country thus easing communication/impact across the Region. Second, Panama is an ideal country for implementation of the programme given its strong governmental support, specifically from the Ministry of Health and Ministry of Education who agreed to commit staff time and infrastructure for this trial.

In sum, the aims of the study are: (1) to test the effectiveness of SFP 10–14 in reducing youth aggressive and hostile behaviour, as reported by parents and adolescents, when implemented via health and educational sites in Panama; (2) to assess the implementation process of SFP 10–14, specifically, implementation fidelity and how these processes vary across sites in order to optimise its scaling up and sustainability should the intervention be shown to be effective; and (3) to assess the cost-effectiveness of SFP 10–14 in Panama.

## Methods/design

This will be a cluster randomised controlled trial (RCT) with two arms: (1) implementation of SFP 10–14 in health and educational services plus services as usual (*n* = 14 clusters); or (2) services as usual only (*n* = 14 clusters). Clusters will be state-owned clinics or schools located in the 28 townships (i.e. *corregimientos* which are political subdivisions within Districts) with the highest homicide rates in the Districts of Panama Centre, Panama East, Panama North and San Miguelito. Out of the 41 townships in these four Districts, the 28 townships with the highest number of homicides per 10,000 inhabitants will be selected for randomisation. The most recent homicide data that will be used are for the years 2015 (whole year) and 2016 (only January until August). The Office of Criminal Statistics (SIEC) at the Ministry of Security will provide homicide data. Size of townships is in the range of 3000–100,000 inhabitants, with an average 8% of the population aged 10–14 years. To reduce contamination, only one site (clinic or school) in any given township will be selected and randomised. A SPIRIT checklist is attached as an Additional file 1 to this manuscript and the SPIRIT Fig. 1 shows the study design.

**Fig. 1 Fig1:**
[figure not shown]
Spirit figure

### Participants

A team of approximately four staff from the Ministry of Health or Education working in selected sites will invite families from those who access their services regularly or more widely from the community to take part in the trial. These staff will be doctors, nurses, psychologists, social workers or health promotion staff in the case of clinics, and teachers in the case of schools. Key inclusion criteria for participation of families in the trial will be: (1) families with a male or female adolescent aged 10–14 years; (2) at least one primary caregiver and one child aged 10–14 years are willing to attend the programme together within a fixed time period; and (3) the ability to speak Spanish (literacy aid will be provided to parents or children who cannot read or write). Key exclusion criteria for participation of families in the trial will be: (1) families in which children and both parents live separately (e.g. the child is in care); (2) families that have participated in SFP 10–14 previously; and (3) families that have taken part in any other family skills training programme in the last 12 months.

### Clusters

Once the 28 townships with the highest rates of interpersonal violence are identified, the administrative counterpart at Ministry of Health (MINSA) will identify a clinic with specialist services for adolescents within each township that meet key inclusion criteria (defined below). These clinics will become clusters for the trial. Only clinics with specialist services for adolescents will be considered for this trial because they are currently the only ones with enough staff for delivering the intervention. In addition, these are the only services that allow consistent access to the adolescent population within townships and have well-established mechanisms for following them up. In the case that there is no clinic with specialist services in a given township, the Ministry of Education (MEDUCA) will be approached in order to identify a suitable school that meets key inclusion criteria. These schools will become clusters for the trial. Clinics and schools have universal reach in townships in Panama.

Key inclusion criteria for a clinic or school to be selected as cluster will be: (1) offering specialist health services or educational services to adolescents aged 10–14 years; (2) being located within one of the 28 townships with highest homicide rates; (3) having at least four permanent staff willing to be trained to recruit families and deliver the intervention; (4) permanent staff available to recruit and deliver the intervention are doctors, nurses, psychologists, social workers or health promotion staff in the case of clinics, and teachers in the case of schools; and (5) having physical space available to deliver the intervention. Key exclusion criteria for not selecting a clinic or school as cluster will be: (1) not offering specialist health services or educational services for adolescents; (2) not having enough staff available to recruit families and deliver the intervention; and (3) not having physical space to deliver the intervention.

### Sample size

For the main trial, the sample size takes into account the intra-cluster correlation coefficient, the maximum cluster size, the expected effect, dropout and the power of the study, and was performed using the *clsampsi* command in Stata. We do not have references to support what the effect sizes would be as this is the first cluster RCT of Familias Fuertes. The effect sizes were chosen as conservative estimates for the ICC. We assumed an intra-cluster correlation of ρ = 0.1 in each arm and a maximum of three groups (30 families) at each site. We assume 90% power for a standardised effect size of 0.5 (based on the primary outcome) with significance level 0.05. The optimum design requires 13 clusters in each arm and 780 families. The estimated dropout rate is 7%. To account for dropout of families, we will recruit an additional site in each arm (we do not anticipate any cluster-level dropout). This leads to a final sample of 28 clusters and 840 families, recruited at baseline. In practice, if a larger ICC is found, this will reduce power to detect the same effect size; an ICC of 0.2 would have 71% power for an effect size of 0.5.

### Recruitment of families

The same recruitment strategy will be used for both arms. Approximately Four selected staff in intervention and control sites will recruit families universally into the study from those who access their services regularly or more widely from the community. Recruitment will take place via referral of families that are accessing services and via open invitations in the community (e.g., in churches and municipalities). These recruiters will be teachers in the case of school sites and nurses, social workers, psychologists, health promotion staff and doctors in the case of clinics. Families in both arms will be compensated at each assessment session to increase retention (USD 4.50 per family). An average hourly wage in Panama is USD 2.47 so compensation will cover 1 h of work plus travel. Families will also receive promotional materials (e.g. keychains, magnets, pens) to increase motivation and retention.

### Randomisation

A minimisation algorithm will be used to ensure balance across arms in terms of: (1) the population size of townships; (2) baseline levels of interpersonal violence in townships; and (3) type of site (e.g. clinic or school). Given that this is a real-world implementation trial that involves training a limited number of staff embedded in selected sites, sites need to be randomised before families are recruited into the study. We are aware randomisation of clusters before recruiting participants can influence recruitment and dropout in the services-as-usual (SAU) arm. To minimise these issues, we have included costs for compensating families per assessment.

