### Blinding

This is an open trial. Research assistants, staff at clusters and families will be aware of participants’ allocated condition during the trial. Those coding data will be un-blinded to group allocation, but those analysing data will be blinded.

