### Intervention condition

Families in the intervention arm will receive SAU plus SFP 10–14. SFP 10–14 will be delivered in groups of approximately ten families (a minimum of six and a maximum of 16 families). The intervention will only be available in selected townships via the trial. In this trial, we will use a ‘universal’ approach in which facilitators will recruit families from the general population and not only those at risk. In other words, they can recruit families from those who access their services generally as well as more widely from the community. The programme comprises seven weekly sessions of 2 h each. Parent and adolescent sessions are conducted separately in the first hour, followed by a second hour together as a family. The first hour focuses on skills, with the second hour designed to recognise family strengths and practice skills covered in the first hour. The intervention addresses three broad areas: family functioning, including communication between parents and children; strengthening parental skills; and helping young people to develop new skills in relation to resisting peer pressure, stress management and goal setting.

MINSA/MEDUCA will select staff to be trained as facilitators of SFP 10–14, trying to identify as much as possible staff who might deliver beyond the trial (i.e. engaged and enthusiastic staff with previous experience working with families). In intervention sites, four staff per site will be trained. We will train 56 new facilitators in two training groups of 28 each. For each training group, three experienced Panamanian trainers will train new facilitators of the intervention. New facilitators will deliver the intervention to a first cohort of families. A cohort is made of one group of approximately ten families per site (140 families in total; ten in each of the 14 sites). After delivery of the intervention to the first cohort of families, the best facilitator per team (i.e. the most committed, empathic, dynamic and with the best skills to manage families) will be trained to become trainer of others. Trainers within each team will be trained to train new facilitators and thus sustain the intervention in the future. Experienced international trainers will be in charge of training trainers.

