### Statistical methods

We will follow CONSORT guidelines for reporting and analysis of cluster RCTs [30, 31]. Participant flow will be reported and analyses will be conducted on the intention-to-treat (ITT) population; all participants randomised will be included regardless of non-compliance with protocol or withdrawal from the study. Analyses will postdate final follow-up assessments, with due consideration of potential biases from loss to follow-up. We will use linear mixed effects models with random intercepts for site and participants will be fitted to the repeated measures to estimate treatment effects for the primary and secondary outcomes. Covariates will include the corresponding baseline outcome measure and minimisation factors. We will allow for missing outcome data under the Missing At Random (MAR) assumption and check the sensitivity of treatment effect estimates to departures from MAR. We will conduct a dose response analysis to estimate effects for number of sessions attended using instrumental variable methods.

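### Families are recruited after site randomisation by staff who know the arm, and the only remedy named for this risk, payment per assessment, does not prevent differential selection of families

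*Protocol article*

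**What the plan says.** **Order and knowledge of allocation.** The Randomisation section explains that, because a limited number of embedded staff must be trained, "sites need to be randomised before families are recruited into the study". The Blinding section adds: "Research assistants, staff at clusters and families will be aware of participants’ allocated condition during the trial".

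**Who recruits.** Under Recruitment of families, "selected staff in intervention and control sites will recruit families universally into the study". The Intervention condition section says that "facilitators will recruit families from the general population and not only those at risk", so in intervention sites the recruiters also deliver the programme. Eligibility (Participants) requires that at least one caregiver and one child "are willing to attend the programme together within a fixed time period".

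**Risk and remedy.** The Randomisation section states: "We are aware randomisation of clusters before recruiting participants can influence recruitment and dropout in the services-as-usual (SAU) arm". The next sentence is the only answer given there: "To minimise these issues, we have included costs for compensating families per assessment". The Recruitment of families section sets the payment at USD 4.50 per family per assessment, equal in both arms, and gives retention as its purpose.

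**Analysis.** The Statistical methods section states: "Covariates will include the corresponding baseline outcome measure and minimisation factors". The minimisation factors are township population, township violence and type of site.

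**The concern.** Randomising sites balances sites in expectation. It does not protect the make-up of the families who enter afterwards if recruiters, or the families themselves, act on knowledge of the arm. Joining also means different things by arm. In an intervention township it is a commitment to seven weekly sessions starting the following week. In a control township it means assessments now, with the programme offered after 12 months only if it proves effective. The willingness criterion may therefore admit different kinds of family in the two arms.

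The protocol sees part of this but replies with a measure aimed at keeping families once enrolled. The primary outcome is parent-reported in an open trial, so differences between arms in family motivation or expected course could be read as a treatment effect, or could mask one.

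**Working it through.** The article gives no figure for imbalance or selection, so there is nothing to reproduce. The check sets the passages side by side and then adds an illustration on assumed values.

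**Step 1: risk against remedy.**
- The admitted risk has two parts, recruitment and dropout, and is confined to the control arm. Selection can arise in either arm, since recruiters know the allocation in both.
- The named remedy is payment at each assessment, whose stated purpose is retention. It answers dropout and may encourage control families to enrol. It has no bearing on whom unblinded staff invite, or on which invited families accept seven sessions.

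**Step 2: safeguards elsewhere in the article.**
- One recruitment strategy for both arms (Recruitment of families). This standardises the procedure but does not blind the recruiters.
- The same information for all families at the first meeting (First meeting with families). The script is conditional: what happens if the township is intervention, and what happens if it is control. Screening, consent and baseline measures follow, and arm-specific invitation cards are described after that. The section does not say that the arm is withheld until the cards are given. The Blinding section says families know their arm during the trial, without saying from when.

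**Step 3: what the named covariates capture.** All three minimisation factors are at township or site level. The baseline value of the outcome is the only family-level covariate named. It covers one important dimension of selection, but not traits such as motivation that bear on the 12-month course at a given baseline score.

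**Step 4: illustration (assumed shifts).** Inputs: 14 clusters per arm and ICC 0.1 (Methods/design, Sample size); 28 families per cluster, from 30 × (1 − 0.07) = 27.9; two-sided 5% test (sidedness assumed).
- Design effect = 1 + (28 − 1) × 0.1 = 3.7.
- SE of the arm difference = √(2 × 3.7 / (14 × 28)) = √(7.4 / 392) = 0.137 SD.
- With no true effect and a residual shift b between arms, the rejection rate comes from the noncentral t distribution with 2 × 14 − 2 = 26 degrees of freedom and noncentrality b / 0.137.

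| Shift at entry (SD, assumed) | Rejection rate, nothing removed | Left if baseline adjustment removes half (SD) | Rejection rate |
|---|---|---|---|
| 0.1 | 10.8% | 0.05 | 6.4% |
| 0.2 | 28.9% | 0.10 | 10.8% |
| 0.3 | 55.7% | 0.15 | 18.3% |

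The SE here is not reduced for covariates. The table shows how sensitive the test is to a shift; it does not estimate what will happen in this trial.

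**The case against.** The order of randomisation is disclosed and justified by the need to train embedded staff. The common strategy and common script are real safeguards, and the written sequence is already close to late disclosure. CONSORT participant flow and measurement of recruitment rates are promised. All of this stands and narrows the point. It leaves open that recruiters know the arm and that no rule fixes when families learn it.

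Several stronger readings are tempting and should not be drawn:
- *Facilitators hand-pick the families they will treat.* Recruitment is described as universal, by referral and open invitation. Research assistants explain the study, and families then decide.
- *Control families are offered assessments only.* They are promised the programme after the final assessment if it is effective.
- *Payment is irrelevant to recruitment.* It is equal in both arms and may help control uptake.
- *Any imbalance passes undiminished into the primary estimate.* Baseline CBCL adjustment removes part of it.
- *The model excludes all other family-level covariates.* The covariate sentence is an open list, and an analysis plan not shown may add to it. The covariate element is therefore secondary.
- *The bias is a known share of the planned 0.5 SD effect.* Any such percentage rests on assumed inputs with no basis in the document.

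A further fair objection is that late disclosure to families leaves recruiters unblinded, and townships may know their arm from the first cohort. The remedy reduces the risk but does not close it.

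**Conclusion.** The point holds in a limited form. The protocol names a recruitment risk, places it in one arm only, and answers it with a retention measure that does not prevent differential selection. The other safeguards are partial. Baseline CBCL adjustment reduces the bias but does not remove it.

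Neither size nor direction can be derived from the document. On the assumed values above, a residual shift of 0.05 SD barely matters (about 6% against 5%), while 0.1 to 0.2 SD would be material (about 11% to 29%). This is a change that should be made because it is cheap and lowers a bias that a larger sample would not remove. It does not show that the trial's result will be biased.

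**What to change.** 1. **First meeting with families:** for families not yet recruited, state that a township's arm is disclosed only after consent and baseline questionnaires, using the existing invitation-card step. The Trial status section reports 285 families recruited and two waves of 280 to come, i.e. 560 of 845, about two thirds. Those waves were expected to start in March 2018, so the rule applies to whoever remains.
2. **Statistical methods:** add adolescent age, sex, and baseline DASS-21 and FRI to the covariates named for the primary model. Age is an eligibility item, and DASS-21 and FRI are listed instruments whose baseline values the secondary analyses already need. That sex is recorded is assumed. Recruitment route should be added only if it is recorded, which the article does not show.
3. **Randomisation:** reword so that payment is presented as a retention measure and selection is acknowledged as possible in both arms.

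**Cost:** a change to the meeting script, a few covariates and two sentences of text. Some intervention families may decline once they learn their arm; they stay in the intention-to-treat set and may dilute attendance. Concealment will be imperfect, because staff remain unblinded and some townships may know their arm from the first cohort.
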